## Abstract

**Background:**

Breastfeeding has countless benefits to mothers, children and community at large, especially in developing countries. Studies from Lebanon report disappointingly low breastfeeding exclusivity and continuation rates. Evidence reveals that antenatal breastfeeding education, professional lactation support, and peer lay support are individually effective at increasing breastfeeding duration and exclusivity, particularly in low-income settings. Given the complex nature of the breastfeeding ecosystem and its barriers in Lebanon, we hypothesize that a complex breastfeeding support intervention, which is centered on the three components mentioned above, would significantly increase breastfeeding rates.

**Methods/Design:**

A multi-center randomized controlled trial. *Study population*: 443 healthy pregnant women in their first trimester will be randomized to control or intervention group. *Intervention*: A “prenatal/postnatal” professional and peer breastfeeding support package continuing till 6 months postpartum, guided by the Social Network and Social Support Theory. Control group will receive standard prenatal and postnatal care. Mothers will be followed up from early pregnancy till five years after delivery. *Outcome measures*: Total and exclusive breastfeeding rates, quality of life at 1, 3 and 6 months postpartum, maternal breastfeeding knowledge and attitudes at 6 months postpartum, maternal exclusive breastfeeding rates of future infants up to five years from baseline, cost-benefit and cost-effectiveness analyses of the intervention. *Statistical analysis*: Descriptive and regression analysis will be conducted under the intention to treat basis using the most recent version of SPSS.

**Discussion:**

Exclusive breastfeeding is a cost-effective public health measure that has a significant impact on infant morbidity and mortality. In a country with limited healthcare resources like Lebanon, developing an effective breastfeeding promotion and support intervention that is easily replicated across various settings becomes a priority. If positive, the results of this study would provide a generalizable model to bolster breastfeeding promotion efforts and contribute to improved child health in Lebanon and the Middle East and North Africa (MENA) region.

**Trial registration:**

Current Controlled Trials ISRCTN17875591

## Background

Despite its countless benefits to children, mothers and community at large, breastfeeding rates in Lebanon continue to be disappointingly low. Previous studies reported acceptable initiation rates varying between 63.8% and 96% [1,2]. However, exclusive breastfeeding is reported in 58.3% of babies less than one month, and in 4.1% to 10.1% of 6-month old infants [3-6]. Only 27.1% of one-year old infants continue to breastfeed [3].

Breastfeeding is associated with reduced infant risk of infections, atopic dermatitis, asthma, obesity, diabetes types 1 and 2, childhood leukemia, sudden infant death syndrome, necrotizing enterocolitis; and with higher Intelligence Quotient and academic performance at 6.5 years of age [7-9]. Moreover, it is associated with decreased maternal risks of diabetes type 2, breast and ovarian cancers, and postpartum depression [7]. As such, breastfeeding is a cost-effective public health measure that has a significant impact on maternal health and infant morbidity and mortality in developing countries [10,11]. Exclusive breastfeeding for 6 months and continued until 11 months of age is the single most effective strategy to improve child survival in developing countries, preventing 13% of under-five mortality [12].

Several cross-sectional studies from Lebanon reported different predictors of low breastfeeding rates. These included lower socio-economic status, Caesarean birth, urban residence, early hospital discharge, mother’s religion, male paediatrician, and hospital practices that hinder breastfeeding like lack of rooming-in of mother and baby, implementing fixed newborn feeding schedules, and offering glucose and water or artificial formula as first feeds instead of breast milk [2,4,13]. A recent qualitative study that explored breastfeeding perceptions and experiences of 36 new mothers who were followed up longitudinally for one year reported several barriers to breastfeeding exclusivity and continuation in the Lebanese context [14]. These included several maternal and community misconceptions such as insufficiency of breast milk and lack of satiety in the baby, breastfeeding causing maternal weight gain or breast sagging, maternal milk being harmful in certain situations such as grief, maternal illness or pregnancy. Moreover, mothers complained of breastfeeding being painful, resulting in sleep deprivation and exhaustion. On the other hand, women who continued breastfeeding for one year were cognizant of the difficulties of breastfeeding and despite this showed determination to succeed and overcome any barrier, relying mostly on family support and proper time management. That study uncovered the need for several interventions that can address the different barriers in the Lebanese context, and the need to empower mothers to overcome them, hoping to improve the existing national breastfeeding exclusivity and continuation rates.

Of the different interventions reported in the literature to improve breastfeeding rates, breastfeeding support, whether professional or lay, was quite effective in increasing breastfeeding duration [15-18]. In particular, lay support with or without a professional component increased the rate of any short- or long-term breastfeeding, as well as the rate of short-term exclusive breastfeeding duration [16]. Lay breastfeeding support has additional health benefits in several aspects of families’ lives such as playing a role in reducing obesity and postpartum depression [17]. Evidence suggests it tends to be more effective in low- and middle-income settings [18]. Similarly, peer support interventions had a significantly greater effect on any breastfeeding in low- or middle-income countries, reducing the risk of not breastfeeding at all by 30%, compared with a reduction of 7% in high-income countries. Moreover, the risk of non-exclusive breastfeeding decreased significantly more in low- or middle-income countries than in high-income countries with these interventions [18]. A recent review of four randomized controlled trials, including one from Syria showed that community-based interventions were significantly associated with an increase in exclusive breastfeeding rates at four and six months after [19]. Interestingly, a mother-to-mother breastfeeding line that was established in Toronto and Nova Scotia to promote and support breastfeeding women succeeded in achieving one hundred percent breastfeeding rate by the end of the third month among the women who participated in The Yarmouth Friendly Feeding Line (YFFL) pilot [20]. Also, a recent Cochrane review that assessed the effectiveness of support for breastfeeding mothers of healthy term babies found that all forms of extra support analyzed together increased the duration of exclusive breastfeeding at 6 months (RR = 0.86; 95% CI: 0.82 to 0.91). Support was more effective in settings with high initiation rates (like Lebanon); with strategies that rely on face-to-face support being more likely to succeed as opposed to support that is offered reactively upon mothers’ request [21].

Breastfeeding education is another intervention that was associated with a significant increase in initiation rates, specifically in low-income USA women as compared to standard of care (RR 1.57, 95% CI: 1.15 to 2.15) [22]. In particular, one-to-one, needs-based, informal repeat sessions, and generic formal antenatal education were effective in increasing breastfeeding rates. Needs-based, informal *peer* support, whether ante-natal or post-natal were particularly effective in increasing initiation rates (RR 4.02, 95% CI: 2.63 to 6.14) [22].

The totality of evidence underscores the heterogeneous and complex nature of breastfeeding barriers in any given setting. Evidence thus suggests that in order to effectively raise breastfeeding rates, there is need for multi-dimensional interventions that simultaneously tackle different aspects of breastfeeding. In this proposed randomized clinical trial, we plan to investigate whether a complex breastfeeding promotion and support intervention starting from early pregnancy is effective in improving six-month breastfeeding exclusivity rates. We hypothesize that a complex intervention composed of several simple interventions that were previously shown to individually improve breastfeeding rates in low- and middle-income countries is more effective than the standard of care in improving breastfeeding exclusivity rate in Lebanon, one of the lowest in the region [23].

Our proposed complex intervention is based on the Social Network and Social Support theory framework, which offers a framework describing pathways through which social ties can influence health [24]. Social networks represent the web of social ties or relationships through which an individual receives social support. Social networks are characterized by the dyadic characteristics of 1) reciprocity, the extent to which support is given and received in a relationship, 2) intensity, the emotional closeness experienced in a relationship, and, 3) complexity, the variety of functions that the relationship serves. In addition, the characteristics of homogeneity in terms of demographic characteristics, geographical dispersion in terms of proximity to the focal person and density in terms of the extent of interaction of members, are used to describe the network as a whole. Social networks represent relationships between people that provide social support as one of their functions. Social support is categorized in four supportive behaviors:

1. Emotional support: conveying that a person is valued and cared for in health promoting ways.

2. Instrumental support: provision of aid and services.

3. Appraisal: provision of information for self-evaluation; constructive feedback.

4. Sharing points of view: offering opinions about how one would handle a situation.

5. Informational support: provision of advice or information to address a particular situation.

Hence, our complex intervention consists of all the following simpler interventions: 1) Offering breastfeeding education and counseling to improve knowledge and expectations; 2) building of appropriate breastfeeding skills to improve self-efficacy and empower breastfeeding mothers; 3) providing professional lactation support; 4) establishing a mother-to mother tree of lay support. This intervention will develop new social network linkages and will use members of women’s own social networks to enhance their role in breastfeeding support.

To our knowledge, this is the first study of its kind to be conducted in Lebanon and the region as no previous studies investigated the effectiveness of a complex intervention composed of several simpler interventions previously shown to improve breastfeeding rates in low- or middle-income countries. Should this intervention prove to be effective, it can be used as a framework for a model intervention that may be replicated in any setting or community in Lebanon, whether rural or urban.

## Methods/Design

### Study design

A randomized controlled single-blind parallel-arm clinical trial to investigate whether a complex intervention targeting new mothers’ breastfeeding knowledge, skills and social support within a Social Network and Social Support theory framework will increase exclusive breastfeeding duration among women in Lebanon.

### Study population

Healthy pregnant women who are in their first or second trimester and who intend to breastfeed after delivery will be eligible to participate in this study.

Women with any of the following conditions will be excluded: pregnancy beyond the second trimester, chronic medical condition, abnormal fetal screen (ultrasound/blood/amniocentesis), not intending to breastfeed, not living in Lebanon for at least six months after delivery, twin gestation, and preterm birth (at <37 weeks gestation).

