#### Randomization

Eligible pregnant women will be randomly allocated to one of two parallel groups (experimental and control, 1:1 ratio), using a computer-generated stratified block randomization that is done by one of the co-investigators (HT) who is not involved in subject recruitment. The size of blocks will vary from 4 to 8 and the stratification will be by study site. Allocation concealment will be done to ensure that group assignment of the patients are revealed only after assessing the inclusion/exclusion criteria are verified and consent obtained. This will be done to avoid any bias that might be introduced by the investigator because of the knowledge of the next allocation group. A set of sequentially numbered opaque sealed envelopes will be prepared with the allocation group, as per the randomization list, specified inside.

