#### Intervention group

Women in the experimental group will, in addition to standard clinical care, receive a complex intervention starting in early pregnancy till 6 months post delivery. The intervention is composed of the following elements: a) prenatal breastfeeding education to raise knowledge and awareness, b) postpartum professional lactation support to improve maternal skills and self-efficacy, c) postpartum peer (lay) support to build social support, and enhance social capital within women’s social networks. These include skill building activities for the provision of effective breastfeeding support.

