### Statistical methods

We will compare continuous variables using Student’s *t* test and categorical variables using Chi square test. The relationship between breastfeeding exclusivity as outcome and the independent variables (maternal age, study group, socio-economic status, maternal education, study site, pediatrician’s gender, type of delivery, baby’s gender, parity, previous breastfeeding, maternal employment, mother’s religion, baseline breastfeeding knowledge and attitude, baseline social support) will be explored in bivariate and multivariate analysis. Regression models will be built to adjust for possible confounding in the relationship between the dependent and the independent variables stated above. All analysis will be done on intention to treat basis. The Statistical Package for Social Sciences (SPSS) will be used for data management and analyses. A p-value of <0.05 will indicate statistical significance.

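### Preterm birth is listed as an exclusion although women are randomised before the third trimester, so it cannot be checked before allocation and, if applied, conflicts with intention to treat

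*Protocol article*

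**What the plan says.** All references are to the protocol article.

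- **Study population**, inclusion: "Healthy pregnant women who are in their first or second trimester and who intend to breastfeed after delivery will be eligible". The abstract gives a narrower window: "443 healthy pregnant women in their first trimester will be randomized to control or intervention group". On either account enrolment comes well before delivery.
- **Study population**, exclusions: the list ends with "twin gestation, and preterm birth (at <37 weeks gestation)". Nothing there says that a previous preterm birth is meant, or that women who go on to deliver preterm stay in the analysis.
- **Randomization**: "Eligible pregnant women will be randomly allocated to one of two parallel groups (experimental and control, 1:1 ratio)". Allocation concealment is described so that "group assignment of the patients are revealed only after assessing the inclusion/exclusion criteria are verified and consent obtained".
- **Intervention group**: women in the experimental arm "receive a complex intervention starting in early pregnancy till 6 months post delivery", so allocation has to precede delivery.
- **Statistical methods**: "All analysis will be done on intention to treat basis".
- **Sample size**: 2% against 12%, 90% power, 5% type I error, 155 per group, raised to 443 for 30% loss to follow-up. Removals for preterm birth are not mentioned.

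**The concern.** An exclusion criterion should be decidable from what is known when the envelope is opened. Birth before 37 weeks is not. Three instructions therefore cannot all be followed: exclude preterm births, verify every criterion before allocation, and analyse by intention to treat.

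What is at stake is who enters the primary comparison. If site staff read the list literally, women leave the trial months after randomisation because of an event that occurs after the intervention has begun. The groups compared are then no longer the groups randomised, and the Discussion acknowledges that team members who deliver the package cannot be blinded. If staff read it loosely, the women stay in. The article does not settle which, so the analysis set for the 6-month exclusivity rate is open to interpretation. Women who are dropped and not followed cannot be recovered later.

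**Working it through.** **1. Logic of the criteria.** The other items that look forward (intending to breastfeed, staying in Lebanon for six months after delivery) can be answered as present intentions at enrolment. Twin gestation and trimester can be established then. Birth before 37 weeks cannot, so as worded the item can act only after allocation.

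**2. Reproducing the stated sample size.** Inputs from Sample size: p1 = 0.02, p2 = 0.12, d = 0.10, 5% type I error (sidedness not stated; two-sided reproduces), 90% power, 30% loss.

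- Without continuity correction: n' = [1.96·√(2·0.07·0.93) + 1.2816·√(0.02·0.98 + 0.12·0.88)]² / 0.10² = 134.7, so 135.
- With continuity correction: n = (n'/4)·[1 + √(1 + 4/(n'·d))]² = 154.1, so **155** per group, as stated.
- 310/0.70 = 442.9, so **443**, as stated.

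The arithmetic is sound. The 443 contains an allowance for loss to follow-up and nothing else.

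**3. Women affected.** The document gives no preterm rate, so this is an assumed range of 5% to 12%.

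- 443 × 0.05 = 22; 443 × 0.12 = 53.
- If they are removed on top of the 30% loss, the evaluable total is 443 × 0.70 × 0.95 = 295 down to 443 × 0.70 × 0.88 = 273, against 310 planned.

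**4. Power if they are kept or dropped.** Assume 10% deliver preterm, that 12% is the rate after term birth in the intervention arm, and that preterm mothers gain no benefit (2%). The all-births rate in that arm is 0.9 × 12% + 0.1 × 2% = 11.0%, against 2%.

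Power with continuity correction replaces n by (√n − 1/(d·√n))² in the usual two-proportion formula. At 155 per arm and 12% against 2% this gives 90.2%, matching the planned 90%.

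| Scenario | n per arm | Rates | Power, no correction | Power, corrected |
|---|---|---|---|---|
| Keep; 30% is loss to follow-up only | 155 | 11% v 2% | 89.9% | 85.1% |
| Drop, on top of 30% loss | 139.5 (= 443 × 0.70 × 0.90 / 2) | 12% v 2% | 91.0% | 86.4% |
| Keep; 30% already covers preterm removals | 172 (= 155/0.90) | 11% v 2% | 92.6% | 89.0% |
| Drop; 30% already covers them | 155 | 12% v 2% | 93.6% | 90.2% |

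The corrected column is the one consistent with the protocol's 155. Under either reading of the 30%, keeping the women costs about 1 point relative to dropping them (86.4 − 85.1 = 1.3; 90.2 − 89.0 = 1.2).

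**The case against.** The strongest reply is that no passage says women who deliver preterm leave the analysis. Intention to treat is stated for everything, and the exclusion could be read as ending participation, or as a history of preterm birth. The first part stands: removal is the consequence of applying the item as an exclusion, not a described procedure. The history reading is possible but unsupported, since the neighbouring items concern the current pregnancy or the woman's present situation and plans. If history was meant, the wording still needs correcting. So the reply limits the finding to a conflict that must be reconciled; it does not remove the conflict.

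Three stronger readings are tempting, and the documents do not support them.

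- *Preterm mothers would be removed more completely from the intervention arm.* Intervention mothers are seen daily in hospital, whereas the first postnatal data contact given for controls is at month 1. But Data collection lists delivery and hospital items at month 1 without separating the arms, and Process evaluation describes the control contacts as similar to those in the intervention group. Earlier contact in one arm does not show more complete ascertainment there.
- *The intervention rate would be inflated from 12% to 13.3%.* That is 0.12/0.90. It needs 10% removed from one arm, none from the other, and no exclusive breastfeeding among those removed. Nothing in the article points to that combination.
- *Keeping preterm mothers would leave power at about 93%.* That holds only without the continuity correction and only if the 30% allowance already includes preterm removals, which Sample size does not say.

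The abnormal fetal screen item can naturally be read as results known at the eligibility check, so it is not a second instance of the problem.

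**Conclusion.** The point holds as a contradiction within the protocol article. Study population contains a criterion that cannot be verified at the time Randomization requires, and applying it would break the intention-to-treat statement in Statistical methods. This needs no outside figure.

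Its size rests on an assumption: at 5% to 12% preterm, about 22 to 53 of 443 randomised women. The bias may be small if the intervention does not affect gestational age and removals are balanced, but neither its size nor its direction can be worked out from the document. Power is not the main issue. The case for correcting the text rests on an undefined analysis set for the primary outcome and an avoidable post-randomisation exclusion.

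**What to change.** In Study population, state that eligibility is fixed at randomisation from information available then, and delete preterm birth from the exclusions. If a previous preterm birth was intended, say so, which makes the item verifiable. In Statistical methods, state that every randomised mother is kept in the primary analysis in her allocated arm, and that an analysis restricted to term births is a sensitivity analysis only.

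If the sponsor prefers to leave preterm births out of the main analysis, it should declare a modified analysis set, have the rule applied identically in both arms by someone blind to allocation, not call that set intention to treat, and state whether the 30% allowance covers these women.

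The cost is a change of wording and some dilution of the effect. With 10% preterm and no benefit in them, continuity-corrected power is about 85% at 155 per arm, or 89% at 172 per arm if the 30% already covers them. That is below or just under the planned 90%, but only about 1 point less than dropping the same women would give.

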### Recruiting process

#### Inclusion of pregnant mothers

Eligible pregnant women will be recruited from two health care centers in Beirut, Lebanon: the Women’s Health Center of the American University of Beirut Medical Center (AUBMC), and the Obstetrics Clinics of Sahel General Hospital (SGH).

#### Randomization

Eligible pregnant women will be randomly allocated to one of two parallel groups (experimental and control, 1:1 ratio), using a computer-generated stratified block randomization that is done by one of the co-investigators (HT) who is not involved in subject recruitment. The size of blocks will vary from 4 to 8 and the stratification will be by study site. Allocation concealment will be done to ensure that group assignment of the patients are revealed only after assessing the inclusion/exclusion criteria are verified and consent obtained. This will be done to avoid any bias that might be introduced by the investigator because of the knowledge of the next allocation group. A set of sequentially numbered opaque sealed envelopes will be prepared with the allocation group, as per the randomization list, specified inside.

